### Data management {19}

The data management plan for this project was reviewed and approved by the Regional Committee for Medical Research Ethics Northern Norway (REC), UiT The Arctic University of Norway, and the data protection officer at UNN-HF. All data will be stored on secure network locations governed by the University Hospital.

### Confidentiality {27}

A study identification code will be allocated to each participant upon entry. Their name, national identity number, or other information that can identify the participant directly will not appear in the research data collected, and the list of identification codes that can be used to identify participants who wish to view, delete or correct their own information or used in other cases where unblinding is needed, will be stored separately and only the project manager will have access to it. According to Norwegian legislation, the list of identification codes must be saved for 5 years after completion of the trial and the data will then be anonymized.

### Plans for collection, laboratory evaluation and storage of biological specimens for genetic or molecular analysis in this trial/future use {33}

Blood is drawn from the participants in the present study as described in a previous study protocol [23], but these data will not be used in the present trial.

## Statistical methods

### Statistical methods for primary and secondary outcomes {20a}

Repeated measures data will be analysed by linear mixed models (LMM) which allow for a combination of fixed and random effects. LMM estimates the parameters using all available patient data and is thus less sensitive to scattered missing data, and has flexible modelling options for the covariance structure of the data [41]. Single means (e.g. baseline data) will be analysed with statistical methods within the framework of general linear models (GLM), if the statistical assumptions for GLMs are met. In case of non-normal data, non-parametric statistics will be performed. SPSS and R will be used for statistical analyses of clinical and cognitive data. Analyses of brain imaging data will be performed in separate programs according to the type of data. FreeSurfer (FS) (https://surfer.nmr.mgh.harvard.edu/) will be used for preprocessing of structural imaging data (volumetric analyses and segmentation), and Tracula inbuilt in FS will be used for DTI data [42], and Permutation Analysis of Linear Models (PALM) will be used to perform statistics on structural data preprocessed in FS, and in analyses where imaging data is combined with other data as covariates or factors [43]. SPM12 (https://www.fil.ion.ucl.ac.uk/spm/software/spm12/) will be used for preprocessing of fMRI data. An alpha value of 0.05 will be used for all analyses, and Bonferroni-corrections will be applied when appropriate for controlling the type-1 error rate.

### Interim analyses {21b}

We do not plan to perform an interim analysis in the present study.

### Methods for additional analyses (e.g. subgroup analyses) {20b}

No additional analyses, including subgroup or adjusted analyses, are planned for this study.

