### Outcomes {12}

The primary outcome measures of this trial are cerebral changes and their association with changes in depressive symptoms and cognitive performance on the N-back task after 2 weeks of daily iTBS or sham iTBS.

Participants will undergo brain imaging prior to and after the iTBS or sham protocol. T1-weighted anatomical cerebral MRI images will be obtained for measures of cortical volume and thickness. Diffusion tensor imaging (DTI) will be used to get data for white matter integrity, whereas fMRI data will be used to obtain functional blood-oxygen-level-dependent (BOLD) data for responses to the N-back task during scanning.

Change in level of depression in measured pre and post-stimulation with the semi-structured clinician-led patient interview MADRS [20] and with the patient-reported BDI-II [21]. Based on the data from Blumberger et al. [8], we estimate a mean decrease of approx. 25% in depressive symptoms over a 2-week treatment course in those receiving iTBS. The minimal clinically important difference (MCID) for BDI-II is suggested to be 17.5% change from baseline and 13% change for the MADRS [27].

Between-group change in working memory and executive functions is measured with performance on a N-back task prior to and after stimulation. The N-back task can be performed on a laptop prior to and after the iTBS stimulation protocol and it is also implemented for use in fMRI [28] We will use 0-back and 2-back tasks that generate measures of the number of correct responses, reaction time, commission and omission errors.

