## Assignment of interventions: allocation

### Sequence generation {16a}

The RCT will be run with an allocation ratio of 1:1 to the two groups (iTBS and sham). We expect a 1:1 ratio of males to females since the groups will be stratified by gender in the randomization.

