## Data collection and management

### Plans for assessment and collection of outcomes {18a}

At baseline, prior to stimulation, a clinical psychologist or a medical doctor will perform a diagnostic assessment using the M.I.N.I [24] and the MADRS [20] in a clinical interview. Information obtained from the participant at baseline includes age, sex, marital status, length of education, living situation, history of depression and comorbidity. The Maudsley Staging Method [31] is used to score the level of treatment resistance. A visual N-back task [32] is performed at a laptop and the BDI-II [21] is a self-report pen-and-paper measure.

The Maudsley Staging Method is a multidimensional model developed to define and stage treatment resistance in unipolar depression. The model maps treatment failures, severity of symptoms and duration of depressive episodes into a continuous score with a cut-off for treatment resistance [31].

The severity of depression symptoms will be evaluated using MADRS and the BDI-II. The MADRS will be administrated pre- and post-stimulation as well as once midway through the stimulation protocol and at close out. BDI-II will be administrated pre- and post-stimulation and again prior to close-out. At all-time points, the outcomes are collected by experienced clinical psychologists or a psychiatrist.

MADRS is a widely used clinician-administered instrument for measuring the severity of depressive episodes in patients with mood disorders. It consists of 10 items rated on a scale of 0 to 6, where higher scores indicate a higher degree of symptoms. MADRS has shown good concurrent validity [33, 34]. The MADRS has shown high correlations with other well-known and widely used clinician-rated scales such as the Hamilton Depression Rating Scale [35], underscoring the MADRS high concurrent validity. Intra-rater reliability was originally reported to be excellent [20]. However, subsequent studies have reported varying intraclass correlation coefficients (ICC). Maier et al. showed total scale score ICCs of 0.73, 0.66 and 0.82 in three separate samples [36]. It has later been demonstrated that the use of experienced clinicians as raters and the use of a structured guide for rating increases the intra-rater reliability. Williams and Kobak found an intraclass correlation for the total scale score between raters on the MADRS of 0.93 [37] whereas Geijer et al. [38] found an inter-rater reliability of ICC = 0.95.

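### The protocol plans no adjusted analyses and names no covariate for its main model, although gender is a randomisation stratum and every outcome has a baseline value; adjusting would add precision at almost no cost.

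*Protocol article*

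**What the plan says.** All of this is in the protocol article.

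- Methods for additional analyses {20b}: "No additional analyses, including subgroup or adjusted analyses, are planned for this study".
- Sequence generation {16a}: allocation is 1:1 and "the groups will be stratified by gender in the randomization".
- Statistical methods {20a}: "Repeated measures data will be analysed by linear mixed models (LMM) which allow for a combination of fixed and random effects". No fixed effects are listed for this model. The same section allows imaging data to be combined with other data as covariates or factors in the permutation software.
- Outcomes {12}: "Participants will undergo brain imaging prior to and after the iTBS or sham protocol".
- Plans for assessment {18a}: "The MADRS will be administrated pre- and post-stimulation as well as once midway through the stimulation protocol and at close out", and "BDI-II will be administrated pre- and post-stimulation and again prior to close-out". The N-back is run before and after stimulation, both in the laboratory and in the scanner.
- Sample size {14}: repeated-measures F-test, f = 0.25, two groups, alpha 0.05, power 0.90, correlation 0.5, giving 46 analysable; with 10% drop-out, 50 to be enrolled.

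**The concern.** A factor used to stratify randomisation would normally appear in the analysis, and a baseline measurement of the outcome is usually the strongest covariate available. Here both are in hand, but the only sentence that mentions adjusted analyses says that none are planned.

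The sizing shows which contrast the authors had in mind. With two time points, a group-by-time test with free baseline means in each arm is the comparison of change scores. That is less efficient than adjusting for baseline whenever the pre-post correlation is below 1. In a trial of this size the loss is worth avoiding, particularly if the true effect is smaller than the one designed for. There is also a question of clarity: a reader cannot tell which models may carry covariates, and leaving that open invites a choice after the data are seen.

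**Working it through.** **Inputs.** From Sample size {14}: f = 0.25, alpha = 0.05, power 0.90, rho = 0.5, N = 46, 50 enrolled, 10% drop-out. The number of measurements, m = 2, comes from the pre/post design. Expected completers: 50 × 0.9 = 45, a derived figure that the article does not state.

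**Step 1. Reproduce the plan's figure.** For a within-between interaction with two groups and two times, the noncentrality is λ = N·f²·m/(1 − rho), with 1 and N − 2 degrees of freedom.

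- N = 44: λ = 44 × 0.0625 × 2/0.5 = 11.0, power 0.8997.
- N = 46: λ = 11.5, power 0.912.

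So 46 is the smallest even N that reaches 0.90, as stated. The between-group main effect would need 130 with the same inputs, so the stated figure is the group-by-time test.

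**Step 2. The implied effect.** Let δ be the difference between arms in mean change, in SDs of a single measurement. The change-score test has λ = (N/4)·δ²/(2(1 − rho)). Equating this with Step 1 gives δ² = 8f² = 8 × 0.0625 = 0.5 per measurement, times m = 2, so δ = 1.0 SD.

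**Step 3. Variance with and without baseline.** In units of the single-measurement variance:

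- change score: 2(1 − rho)
- adjusted for baseline: 1 − rho²
- ratio: (1 − rho²)/(2(1 − rho)) = (1 + rho)/2

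| rho | variance ratio | unadjusted variance relative to adjusted |
|---|---|---|
| 0.3 | 0.65 | 1/0.65 = 1.54 |
| 0.5 (plan) | 0.75 | 1/0.75 = 1.33 |
| 0.7 | 0.85 | 1/0.85 = 1.18 |
| 0.9 | 0.95 | 1/0.95 = 1.05 |

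**Step 4. Power at 45 completers (23 and 22), rho = 0.5.** The adjusted test divides the variance as above and loses one degree of freedom.

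| true difference in change | unadjusted | baseline-adjusted |
|---|---|---|
| 1.0 SD (design) | 0.906 | 0.966 |
| 0.8 SD | 0.746 | 0.857 |
| 0.5 SD | 0.374 | 0.473 |

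At 1.0 SD, the N needed for 90% power falls from 46 to 34. A simulation of 4,000 trials at N = 46 agrees: 0.915 unadjusted, 0.966 adjusted.

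**Step 5. Gender.** If gender explains nothing, adding it costs one degree of freedom and power at 45 stays at 0.966. If it explains 5% of the residual variance (an assumed figure), power is 0.973.

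The effect of leaving it out on the type I error of the change-score test was simulated (20,000 runs, n = 48 balanced, rho = 0.5). With gender shifting the pre and post scores equally, by 0.5 or 1.0 SD, the error rate is 0.048 and 0.049, so a stable gender difference cancels. With gender shifting only the post score by the same amounts, it is about 0.043 and 0.028.

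**The case against.** **The sentence may not bind the main model.** It stands under additional analyses, where adjusted analyses are listed as one kind of extra. The main models are described in {20a}, and their fixed effects and baseline parameterisation are details that an analysis plan, not shown here, would normally hold. This stands in part. A reader might infer that the protocol forbids any adjustment, and the document does not go that far. But the point does not rest on silence: the article says without qualification that adjusted analyses are not planned, and its sample size is that of the unadjusted test.

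**Baseline is not discarded.** The mixed model carries it as a repeated outcome. This stands. The loss in Step 3 arises only if baseline means are left free in each arm. A model that constrains them to be equal recovers about the same precision as a baseline covariate, and the article does not say which is meant.

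**A reader might infer that leaving out the stratum makes standard errors too large.** The documents do not support this. Step 5 shows that it happens in a change-score test only if gender predicts change, and nothing in the article shows that it does.

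**A reader might also infer that the trial is underpowered for want of adjustment.** It is not, on its own assumptions: 0.906 at 45 completers meets the stated 90%.

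**The correlation of 0.5 is given only for the N-back fMRI analysis.** This stands. If structural measures such as cortical thickness or fractional anisotropy correlate more highly before and after treatment (an assumption), the gain shrinks to about 5% in variance at 0.9. The association aims are not simple group contrasts, so these figures do not carry over to them.

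**The covariates foreseen in {20a} may be variables of interest,** such as symptom change related to cerebral change, and so need not contradict {20b}. This is fair: the two sections sit uneasily together but can be reconciled.

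**Conclusion.** The concern holds as a matter of efficiency and clarity. The article plans no adjusted analyses and names no covariate for the main model, while the stratification factor and the baseline of every outcome are available. If the group-by-time test is used as sized, with free baseline means, the contrast carries one third more variance than it needs to at the plan's correlation.

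The gain is material if the true effect falls short of the design value of 1.0 SD and modest if it does not; it fades for outcomes with high pre-post correlation. The case for including gender is that the analysis should match the randomisation; it does not rest on a demonstrated loss of precision or error control.

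The figures assume two measurements with equal variances, the difference in change held fixed in raw SD units, and 45 completers.

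**What to change.** In Statistical methods {20a}, state that the main between-group models include gender as a fixed effect, together with either the baseline value as a covariate or baseline means constrained equal across arms. Use gender and the corresponding baseline measure in the imaging group comparisons where feasible.

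In {20b}, keep the commitment to no subgroup analyses but remove the exclusion of adjusted ones, so that it agrees with the covariates foreseen in {20a}. Report the unadjusted results as a sensitivity analysis. Settle this before allocation is revealed to the analysts.

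The cost is wording, one or two degrees of freedom, and no new data. The imaging models need somewhat more set-up, since a baseline covariate there may have to be specific to each location.

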### Methods in analysis to handle protocol non-adherence and any statistical methods to handle missing data {20c}

Protocol non-adherence will be addressed using an intention-to-treat analysis, which includes all participants as originally allocated regardless of adherence. Missing data will not be imputed. Missing data will be reported in the manuscripts. Sensitivity analyses will be conducted to evaluate the impact of different missing data assumptions, such as missing not at random.

### Plans to give access to the full protocol, participant-level data and statistical code {31c}

We plan to make the dataset and the statistical code available on the Open Science Foundation (OSF) after the study is published.

## Oversight and monitoring

### Composition of the coordinating centre and trial steering committee {5d}

This trial will be conducted in a manner consistent with good clinical practice. Principal Investigator [name] is responsible for the overall conduct of the trial. [name] coordinates the daily operations of the study in cooperation with the principal investigator and project manager at UIT, [name] the responsible MD. [name]. [name] and [name] oversee all research activities daily. Group meetings are held monthly. Only trained healthcare personnel interact with the participants.

### Composition of the data monitoring committee, its role and reporting structure {21a}

A Data Monitoring Committee has not been established. There is reasonable evidence for the effect and safety of the iTBS protocol used and the superiority of active compared to sham iTBS.

### Adverse event reporting and harms {22}

Any serious adverse events will be reported to the Regional Research Ethics Committee of Northern Norway and the University Hospital of North Norway immediately. If any participant suffers harm from participating in this study, they will receive medical treatment as required as a public patient.

### Frequency and plans for auditing trial conduct {23}

The study is conducted in accordance with good clinical practice and in accordance with the recommendations from the Regional Research Ethics Committee, Northern Norway. Participants in the study are cared for by experienced healthcare professionals bound by confidentiality. All data will be stored on secure network locations governed by the university hospital accessible only to project group members and protected by two-factor identification. The data management plan for this project was reviewed and approved by the Regional Research Ethics Committee, Northern Norway and the data protection officer at UNN-HF.

### Plans for communicating important protocol amendments to relevant parties (e.g. trial participants, ethical committees) {25}

In the event of protocol changes, the Regional Research Ethics Committee, Northern Norway will be notified in advance of making changes and updates will thereafter be published in ClinicalTrials.gov.

### Dissemination plans {31a}

The primary audience for this project includes scientific communities involved in psychiatry, clinical psychology, neuroscience, and non-invasive brain stimulation. Additionally, organizations in the field of psychiatry and stakeholders within the healthcare sector are considered valuable recipients of the project’s outcomes. Given the significant societal impact of innovative depression treatments, the general public is also regarded as an important audience.

The research findings will be disseminated through publication in peer-reviewed, open-access scientific journals. Collaborating closely with the media department at UiT, we aim to publicly share the results and provide general information about the project. Furthermore, the research group plans to actively participate in relevant scientific conferences and intends to apply for hosting symposiums focused on iTBS and depression treatment.

## Discussion

The present study protocol outlines the scientific rationale for a randomized, double-blind, parallel-group, sham-controlled neuroimaging trial. This trial aims to investigate the neurocognitive effects of intermittent theta burst stimulation (iTBS) on unipolar depression in patients referred to the psychiatric outpatient clinic at the University Hospital of North Norway.

Understanding the neurocognitive changes induced by iTBS is crucial for several reasons: first, to elucidate the mechanisms underlying iTBS; second, to determine how cerebral changes after iTBS relate to cognitive and antidepressant outcomes post-treatment and third; to inform patient selection for a therapy that holds promise for improvement of cognitive control functions in depression.

To date, few studies have assessed how iTBS affects cerebral grey or white matter structural integrity through pre- and post-treatment MRI examinations. This neuroimaging study boasts several strengths, including a placebo control and a relatively large sample size.

The study has the potential to provide novel scientific insights into the treatment effects of iTBS, a promising and currently considered safe treatment option for depression. Furthermore, it will be among the few studies to elucidate the neurocognitive mechanisms of iTBS and its potential to enhance neurocognitive function in depression.

## Trial status

This manuscript is based on the trial protocol dated August 13th 2024. At the time of submission, patient recruitment has begun, and it is estimated to be completed by 30 June 2025.

## Data availability {29}

All publications will be open access as required by the funding agency. The data management plan for this project was reviewed and approved by REC, UIT and UNN-HF. The complete data file with anonymized data will be stored at the UIT open data repository (https://dataverse.no) after the publications from this trial are published. Authorship will follow the Vancouver guidelines.

## Abbreviations

iTBS: Intermittent theta burst stimulation
HF rTMS: High-frequency repetitive transcranial magnet stimulation
LDLPFC: Left dorsolateral prefrontal cortex
ACC: Anterior cingulate cortex
RACC: Rostral anterior cingulate cortex
RMT: Resting motor threshold
MRI: Magnetic resonance imaging
fMRI: Functional magnetic resonance imaging
FA: Fractional anisotropy
RCT: Randomized controlled trial
WM: Working memory
EF: Executive functions
MADRS: Montgomery Aasberg Depression Rating Scale
BDI-II: Beck Depression Inventory II
DTI: Diffusion tensor imaging
LMM: Linear mixed model
ANOVA: Analysis of variance
ANCOVA: Analysis of covariance
GLM: General linear model
LMM: Linear mixed models
MNI: Montreal Neurological Institute
M.I.N.I.: Mini-International Neuropsychiatric Interview
UIT: University of Tromsø – The Arctic University of Norway
UNN-HF: University Hospital of North Norway – Health Trust
PALM: Permutation Analysis of Linear Models
RMT: Resting motor threshold
FS: FreeSurfer
ICC: Intraclass correlation
MCID: Minimal clinical important
BOLD: Blood oxygen level dependent
